### Individual patient-level analyses

Mixed effects logistic regression will be used to assess the effect of EPaCCS on the primary and secondary outcome measures adjusting for covariates associated with these outcomes such as the availability of carers, social determinants of health (age, gender, ethnicity, social deprivation), marital status, living circumstances, place of care and comorbidity. To account for the time-varying nature of implementation, the season/financial quarter will also be included in the model. Marginal ORs for each of the outcomes based on weighted logistic regression will be reported.

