### Work package 2: evaluation of the effect of EPaCCS on place of death and secondary healthcare use at end of life and cost minimisation analysis of EPaCCS (objectives 2A and 2B)

The second work package will adopt a retrospective cohort design under a natural experiment framework to evaluate the effects of EPaCCS on quality indicators of end-of-life care. The quality indicators used in this work package include the place of death (primary outcome) and time spent in hospital in the last 90 days of life (secondary outcome).^48^ The hypothesis for work package 2 is that people with EPaCCS records are less likely to die in hospital and more likely to spend less time in hospital in the last 90 days of life compared with people without EPaCCS records. An EPaCCS record may address one or both sides of the cost-effectiveness ratio; reducing futile or unwanted treatments will save hospital resources while improving goal-concordant care realises more utility. However, there is also the potential for increased costs, notably through substitution effects, for example, if people die in a hospice instead of in a hospital. We therefore hypothesise that EPaCCS improve the cost-effectiveness of care near the end of life.

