Using the CMC-WSIC linked dataset and the Leeds dataset, the study will use a natural experiment approach^33^ and establish cohorts of patients who have died having EPaCCS (case) or not having an EPaCCS (control) in each dataset separately. Place of death will be coded as a binary variable for individual-level analysis, indicating whether death occurred in a hospital or elsewhere. For ecological analysis, rates of hospital deaths per year will be calculated for each one of the eight health boroughs (previously called CCGs) in North West London. Time spent in hospital will be derived as a continuous variable measuring the number of days between admission and discharge within the last 90 days of life, or between admission and death for patients who died in hospitals. Rates of time spent in hospital within the last 90 days of life per year will also be calculated. The cost analysis will use the patient-level cost data available in WSIC. Formal costs will be estimated by combining utilisation frequencies in the data with unit costs for different services.^49^ Informal care hours will be estimated from the literature on end-of-life care populations and associated costs using the substitution method (primary analysis) and opportunity cost method (sensitivity analysis). Intervention costs will be estimated using NHS data.^50^ We will model costs after diagnostic testing of different modelling approaches in the context of distributional characteristics.^51^

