### Creating comparative cohorts

This study will take an inclusive approach to defining the cohorts for inclusion in the individual-level analysis, identifying deceased patients who had mention of one of the four main disease-related causes of death in their clinical records within the last year of life (cancer, dementia, heart or lung disease). Based on previous analyses^52^ and publicly available national data,^53^ we hypothesise that 22–30% of the EPaCCS cohort will die in the hospital compared with 45–50% in the non-EPaCCS group. The inverse probability of treatment weighting will be used to account for the confounding resulting from the non-random allocation of EPaCCS to the groups and balance characteristics between cohorts.^54^ First, a multivariable logistic regression will be used to determine the propensity score weights. Factors included in the model to estimate propensity scores will include the confounders selected to be included in the main outcome analysis (such as age, sex, ethnicity, deprivation and primary diagnosis). These confounders will be cautiously selected based on thorough discussions with our team, which includes experts in palliative care, input from the patient and public involvement group with lived experience in end-of-life care, and a comprehensive literature search. Then, for each patient inpatient encounter, a weight defined as the inverse of the probability of the treatment they had received will be calculated. The balance of patients’ characteristics will be assessed visually and by examining the standardised mean differences.^55^

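### Hospital time is defined as a continuous number of days but assigned logistic regression and odds ratios with no cut-point; for place of death, the mixed and weighted models are not related to each other

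*Protocol article*

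**What the plan says.** The work package 2 section of the protocol article names two quality indicators: "the place of death (primary outcome) and time spent in hospital in the last 90 days of life (secondary outcome". It then gives each a scale. For the primary outcome: "Place of death will be coded as a binary variable for individual-level analysis, indicating whether death occurred in a hospital or elsewhere". For the secondary outcome: "Time spent in hospital will be derived as a continuous variable measuring the number of days between admission and discharge", counted within the 90-day window, "or between admission and death for patients who died in hospitals".

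Under Creating comparative cohorts, the article turns to confounding: "The inverse probability of treatment weighting will be used to account for the confounding resulting from the non-random allocation of EPaCCS".

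Under Individual patient-level analyses, one model is assigned to both outcomes: "Mixed effects logistic regression will be used to assess the effect of EPaCCS on the primary and secondary outcome measures". That model also includes patient covariates, among them carer availability, demographic and deprivation measures and comorbidity, plus season or financial quarter. The same paragraph ends: "Marginal ORs for each of the outcomes based on weighted logistic regression will be reported".

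**The concern.** There are two separate problems, and they differ in weight.

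The first is a contradiction about the secondary outcome. Only two outcomes are named, so a model for the primary and secondary measures, and an odds ratio for each of them, must include hospital days. A number of days has no binary logistic model and no odds ratio until someone turns it into a yes/no or ordered variable, and the article does not do so. The analyst must depart from the stated model or invent a cut. Work package 2 has a directional hypothesis that people with EPaCCS records spend less time in hospital. A cut chosen after the data have been examined is open to selection on exactly that hypothesis, and any single cut discards most of the information in the day count.

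The second is an ambiguity about the primary outcome. The treatment coefficient of a covariate-adjusted mixed logistic model is conditional on the covariates and the cluster. The odds ratio promised for reporting is marginal and comes from a weighted model. The text does not say whether these are one model or two, or which gives the main result. An analyst who put weights and covariates into a single model would obtain a conditional odds ratio under a marginal label.

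**Working it through.** **Hospital days: the passages side by side.**

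- Scale of the outcome (work package 2 section): continuous, in days, within the last 90 days of life.
- Model (Individual patient-level analyses): mixed effects logistic regression.
- Effect measure (same section): marginal odds ratio for each outcome.
- Cut-point or categories: none anywhere in the article.
- Clauses that leave the model open: the diagnostic testing of alternative models applies to costs, and the remark that other approaches will be considered sits under Ecological analysis. Neither covers the individual-level analysis of hospital days.

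As a mechanical check, a binary logistic fit to a simulated count of 0 to 90 days was rejected because the outcome must lie between 0 and 1. The article gives no distribution of hospital days, so no size can be put on the loss from dichotomising.

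**Place of death: are the two odds ratios the same quantity?** The article states no odds ratio to reproduce. It does give expected hospital-death proportions under Creating comparative cohorts: 22–30% with EPaCCS and 45–50% without.

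Step 1. Crude odds ratio, OR = [p1/(1−p1)] / [p0/(1−p0)]:

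- 22% v 50%: (0.22/0.78)/(0.50/0.50) = 0.28
- 30% v 45%: (0.30/0.70)/(0.45/0.55) = 0.52
- mid-points, 26% v 47.5%: (0.26/0.74)/(0.475/0.525) = 0.39

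These come from group proportions, so they are on the marginal scale.

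Step 2. Conditional odds ratio that matches the same marginal proportions. Assume covariates and cluster together act as a normal effect with standard deviation s on the logit scale. For each group, solve E[expit(b + sZ)] = p for b, with Z standard normal; the conditional OR is exp(b1 − b0). The article gives no value of s, so a range is shown for the mid-points:

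| Assumed s | Marginal OR | Matching conditional OR |
|---|---|---|
| 0.5 | 0.39 | 0.37 |
| 1.0 | 0.39 | 0.32 |
| 1.5 | 0.39 | 0.27 |
| 2.0 | 0.39 | 0.22 |

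Step 3. Which model gives which quantity? This was simulated with n = 400,000 and one standard normal confounder L. The assumed model is logit P(exposed) = 0.8L and logit P(hospital death) = −0.1 − 1.0 × exposure + 1.5L. The true conditional OR is exp(−1.0) = 0.368 and the true marginal OR is 0.490.

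| Fitted model | OR |
|---|---|
| Inverse-probability-weighted, exposure only | 0.484 |
| Adjusted for L, unweighted | 0.363 |
| Weighted and adjusted for L | 0.362 |

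The weighted model without covariates recovers the marginal OR. Adding the covariate returns the conditional OR, even with the weights in place. The simulation has no random effect; a random effect is a further term to condition on.

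**The case against.** The best defence is that this is a condensed article, a full statistical analysis plan is promised under Reporting guidelines, and the objective is framed as exploratory. Leaving a model to that plan would be no fault. Here, however, the article has not left it open: it fixes a model and an effect measure that its own outcome definition does not admit, so a later plan must contradict one or the other. The exploratory framing lowers the severity but does not remove the conflict.

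A second defence is that days out of 90 could be treated as a fraction and fitted with a fractional or grouped logistic model. That is possible, but the article describes a continuous number of days and nowhere a proportion.

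For place of death, the defence largely succeeds. A reader might infer that neither stated estimate can be produced, or that a conditional odds ratio will be reported as marginal. The text does not support that. It bases the marginal odds ratios on weighted logistic regression, and Creating comparative cohorts supplies the weights. For a binary outcome that route works, as the simulation shows, and a mixed model can be fitted beside it. What stands is only that the relation between the two models is unstated.

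A reader might also infer two further faults:

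- **Costs.** The cost analysis might seem to lack a day or risk difference to feed it. Costs are to be modelled from patient-level cost data and from utilisation with unit costs, and nothing says they draw on these odds ratios.
- **The day-count rule.** It might seem to credit hospital deaths with the terminal stay only. The more natural reading is that death replaces the missing discharge date for the final stay. How to count a stay that straddles the start of the window is ordinary derivation detail.

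**Conclusion.** The secondary-outcome analysis is wrong as written. The work package 2 section and Individual patient-level analyses conflict on hospital days, and the conflict cannot be settled from the article without an unplanned cut or a different model. This conclusion rests on the text alone and needs no assumed figure.

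The primary-outcome analysis can be carried out, but its main estimand is not clearly identified. How far this matters depends on how strongly the covariates and cluster predict place of death. At the mid-point proportions, a marginal odds ratio of 0.39 corresponds to a conditional one between 0.37 and 0.22 for assumed standard deviations of 0.5 to 2.0. These figures illustrate the gap and do not predict the result; the 0.39 itself is crude, before any control of confounding.

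Severity: should be fixed before analysis. It does not undermine the primary comparison.

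**What to change.** Under Individual patient-level analyses:

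1. Restrict logistic regression and odds ratios to place of death.
2. Analyse hospital days with an inverse-probability-weighted model suited to a bounded count that probably has many zeros, such as a two-part (hurdle) or negative binomial model, and report the marginal difference in mean days. A negative binomial model does not respect the upper limit of the window, so its fit near that limit should be checked. A mean-days scale also sits better beside the ecological analysis, which uses aggregate hospital time over total deaths.
3. For place of death, state that the marginal odds ratio comes from the weighted logistic model without outcome covariates, or from standardisation of the adjusted model. Label the covariate-adjusted mixed-model odds ratio as conditional and supportive.

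If the team does want a yes/no version of hospital time, the cut should be fixed and justified before data access and reported as an additional analysis.

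The cost is a few sentences, slightly more programming and a change of effect measure for the secondary outcome. No further data are needed.

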*The NHS Long Term Plan* advises building a ‘digital front door’ connecting health professionals to people^24^ to improve access, coordination, health outcomes and efficiency.^25^ In line with this, ACP records need to be accessible to healthcare professionals across different settings.

Electronic Palliative Care Coordination Systems (EPaCCS) have been specifically designed to facilitate seamless electronic information sharing and enable ACP and end-of-life care decision-making to increase the likelihood of delivering end-of-life care following patient wishes and priorities.^26^,^28^ EPaCCS records are intended for creation by trained healthcare professionals with input from patients and their carers to enable patients to discuss and make decisions about their preferences for end-of-life care such as preferred place of death, the ceiling of treatment and resuscitation status. Once stored, it is expected that information should be shared electronically with different professionals across different settings to inform decision-making, especially in times of crisis (emergency services (NHS 111 and 999), general practice, specialist palliative care services, hospices, etc).^26 27^ Nationally, 175 (83%) clinical commissioning groups (CCGs), now Integrated Care Boards (ICBs), have either implemented EPaCCS or started planning for their implementation.^29^ The Department of Health’s National Commitment for End-of-Life Care has recommended continued EPaCCS roll-out^30^ and they have been endorsed in the ‘Palliative and End-of-Life Care: Statutory Guidance for Integrated Care Boards (ICBs)’.^31^

While EPaCCS offer potential merits, no UK research has yet evidenced (1) to what extent EPaCCS support advance care planning, (2) to what extent EPaCCS have been offered equitably to all those who stand to benefit from them, (3) the effect of EPaCCS on patients’ place of death, and (4) if EPaCCS are associated with the use of health resources at the end of life where care costs are high.^32^

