### Data sources

The study will use non-identifiable data from three EPaCCS across three distinct geographical locations in the UK, namely London, Leeds and Bradford, which combined have a population of 10.4 million people. These EPaCCS were introduced at different times within the same city and across different cities. This has led to natural variation in exposure, resulting in datasets that cover varying time periods: 2010–2022 in London, and 2015–2023 in Leeds and Bradford. Nonetheless, these EPaCCS are well established and contain a sufficient number of records, as illustrated in table 1, to enable meaningful individual site analyses and answer our research questions. Additional anonymised EPaCCS data from different regions will be considered if made available during the study. The sample size will be determined by the data available in the three datasets and will vary depending on the analysis.

**Table 1 T1:** EPaCCS and data availability

EPaCCS location	EPaCCS specific data
London EPaCCS	Coordinate My Care (CMC) served as the commissioned EPaCCS in London from 2010 to 2022, during which time it was also the largest UK EPaCCS. Covering 32 CCGs serving a population of 8.9 million, this EPaCCS dataset reflects a diverse urban patient population in terms of diagnosis, ethnicity and socioeconomic background. CMC records comprise data from various healthcare settings, including primary and secondary care, hospices and nursing homes. The dataset encompasses demographics, diagnoses, care preferences, the ceiling of treatment, resuscitation status, living circumstances, prognosis, performance status, date and place of death. Additionally, data is available regarding how often the record was accessed by urgent and non-urgent healthcare workers. In later years, patients had the option of starting a ‘MyCMC’ plan, whereby they use a patient portal to input some data themselves. The anticipated numbers for inclusion in the dataset are 140 000 records, of which 100 000 are for deceased patients.

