The study will describe how EPaCCS are used, specifically who creates EPaCCS records and what information they encompass regarding individuals’ preferences for end-of-life care. The study will describe data fields across each of the three datasets and evaluate their completeness. Additionally, a descriptive analysis of the three EPaCCS datasets will be undertaken to describe the creation and content of the records across the three regions. These specific regions were chosen for being large metropolitan areas with varied levels of material deprivation and a high concentration of ethnic minority groups. This analysis will focus on the elements of ACP used to support decision-making at the end of life, which include documentation of the ceiling of treatment, resuscitation status, preferred place of care and preferred place of death. The study will also explore if changes are made to decision-making over time for each of these elements. As the three EPaCCS in the study contain data from different periods in time, we will take into account the different timescales during the analyses. The uptake of EPaCCS will be evaluated by describing the number of records created across different time periods and locations. The study will also investigate the setting of the initial record creation (hospital care, primary care, community care). Furthermore, the study will describe the clinical characteristics of patients such as their diagnosis, performance status, capacity for decision-making, living arrangements and expected prognosis. The study will also describe their socio-demographic characteristics with a particular emphasis on social determinants of health such as age, gender, socioeconomic position and ethnicity. The socioeconomic position will be defined using the Index of Multiple Deprivation (IMD), a standard scoring system based on a range of economic, social and housing data, creating a single deprivation score for each small area of the country. Using methodology previously employed in studies by the research team,^43 44^ an IMD score will be created for each patient based on their postcode which will reflect the deprivation data for the Lower-layer Super Output Area (LSOA) within which the postcode falls. Moreover, the study will investigate across sites the association between social determinants of health and the completion of each of the four previously mentioned ACP elements. Table 2 shows the mapping of the study objectives to data sources and eligibility criteria. Exclusion criteria for all data sources are participants who have chosen National Data Opt-Out and those who have withdrawn consent.

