### Missing data considerations

Individual-level missing data of the primary outcome variable (place of death) will be excluded from the multivariable analysis. However, in handling missing data related to covariates, those with incomplete data will be identified for a thorough characterisation of the missingness. Depending on the type of data and the level and mechanism of missingness, individual patients without matching covariate data may be excluded from the multivariable modelling. In doing so, we would also be mindful that by excluding such patients, modelling could be subject to biases, for example, due to under-reporting. Hence, we may consider imputing missing data, with sensitivity analysis to determine the effectiveness of imputation on the model outputs.

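### Place of care is an adjustment covariate with no requirement that it precede the EPaCCS record; a value measured after record creation is a mediator and biases the total effect in objective 2A

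*Protocol article*

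**What the plan says.** The section on individual patient-level analyses specifies mixed-effects logistic regression for the primary outcome (hospital death) and the secondary outcome (time in hospital in the last 90 days). It describes the model as "adjusting for covariates associated with these outcomes such as the availability of carers", and the list goes on to "marital status, living circumstances, place of care and comorbidity". No definition or measurement date is given for place of care. The effect to be reported is a marginal odds ratio from weighted logistic regression.

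The section on creating comparative cohorts defines the weights: "Factors included in the model to estimate propensity scores will include the confounders selected to be included in the main outcome analysis". Its examples are age, sex, ethnicity, deprivation and primary diagnosis. It adds that confounders will be chosen with care, using clinical experts, patient and public input and a literature search.

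On what EPaCCS are for, the Introduction says that they are designed to "increase the likelihood of delivering end-of-life care following patient wishes and priorities". Work package 1 lists the advance care planning elements held in the record as "documentation of the ceiling of treatment, resuscitation status, preferred place of care and preferred place of death". Work package 2 hypothesises the following: "people with EPaCCS records are less likely to die in hospital and more likely to spend less time in hospital in the last 90 days".

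**The concern.** Objective 2A asks for the effect of EPaCCS on place of death and hospital use, which is a total effect. The protocol expects EPaCCS to work by steering care to the setting the patient wants. If place of care describes where the patient was looked after once the record existed, it lies on the path from EPaCCS to place of death. Conditioning on it, or weighting so that the groups are balanced on it, compares patients as though EPaCCS had not changed the setting. What remains is closer to a direct effect that bypasses place of care.

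For the secondary outcome the problem is more immediate. Being cared for in hospital late in life is close to the same measurement as days in hospital in the last 90 days.

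The selection rule offers no protection. Association with the outcome is a property that mediators share with confounders. What separates them is timing relative to exposure, and the protocol does not use timing as a criterion. The study aims at credible causal estimates and at recommendations on continued EPaCCS use, so a real benefit could be reported as small or absent.

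**Working it through.** **What the protocol gives.** It states no adjusted effect and no power calculation, so there is no figure of its own to reproduce. It does hypothesise hospital-death rates of 22–30% with EPaCCS and 45–50% without (section on creating comparative cohorts). About half of Leeds decedents have had a record since 2019 (Table 1), which supports a 50:50 split.

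**Hypothesised contrast without place of care in the model.**
- Smallest: 30% v 45%, OR = (0.30/0.70)/(0.45/0.55) = 0.52, difference 15 points.
- Largest: 22% v 50%, OR = (0.22/0.78)/(0.50/0.50) = 0.28, difference 28 points.
- Mid-range: 26% v 47.5%, OR = (0.26/0.74)/(0.475/0.525) = 0.39, difference 21.5 points.

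**Effect of weighting on a mediator.** Let M = 1 if the place of care is hospital. Let a and b be the risks of hospital death in controls with M = 1 and M = 0, and s the share of the risk difference that passes through M. The values of a, b and s are assumptions; the documents give none.
1. Controls with M = 1: m0 = (0.475 − b)/(a − b).
2. EPaCCS patients with M = 1: m1 = m0 − s × 0.215/(a − b).
3. A common conditional OR is solved so that the overall EPaCCS risk stays at 26%.
4. Weighting on M gives both groups the pooled M distribution, m = (m0 + m1)/2. The weighted risk in each group is m × risk(M = 1) + (1 − m) × risk(M = 0).

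Worked case, a = 0.90, b = 0.10, s = 0.50:
- m0 = 0.375/0.80 = 0.469; m1 = 0.469 − 0.1075/0.80 = 0.334; m = 0.402.
- The conditional OR that returns 26% is 0.28, giving EPaCCS risks of 0.717 (M = 1) and 0.030 (M = 0).
- Weighted EPaCCS risk: 0.402 × 0.717 + 0.598 × 0.030 = 0.306.
- Weighted control risk: 0.402 × 0.90 + 0.598 × 0.10 = 0.421.
- Marginal OR = (0.306/0.694)/(0.421/0.579) = 0.61; difference 11.5 points.

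Range over a/b of 0.95/0.05, 0.90/0.10, 0.80/0.20 and 0.70/0.25:

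| Share through place of care | Marginal OR | Risk difference (points) |
|---|---|---|
| 0% | 0.39 | 21.5 |
| 25% | about 0.48 | about 17 |
| 50% | 0.60–0.62 | 11–12 |
| 75% | 0.77–0.79 | 5.5–6 |
| 100% | 1.00 | 0 |

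The size depends on the share mediated and hardly at all on how strongly place of care predicts place of death.

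**Checks on direction (all inputs assumed).**
- Conditional OR: with a/b = 0.95/0.05 and 75% mediated it is 0.30, further from 1 than the marginal 0.39. This is non-collapsibility, not a larger effect.
- An unmeasured common cause of place of care and place of death, with no direct effect: total ORs of 0.62–0.70 become 0.89–1.13. With an opposing direct effect, one total OR of 0.88 becomes 1.45.
- Place of care as a pre-EPaCCS confounder: crude ORs of 0.48–0.70 return to the true 0.61–0.62 after adjustment. In that case adjusting is correct.

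**The case against.** The strongest reply is that the protocol never says place of care means care near death. It stands beside carers, marital status and living circumstances, which are mostly background characteristics, and could mean a usual setting such as a care home before any record existed. Adjustment would then be right. This stands in part: the text leaves the timing open, so a reader should not infer that the covariate is certainly a consequence of EPaCCS. The reply does not dispose of the point. The time windows named in work package 2 (last 90 days, last year of life) are anchored on death, living circumstances is listed separately, and nothing confines covariates to pre-exposure values.

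It can also be said that the covariate list is illustrative, that confounders are to be chosen carefully, that sensitivity analyses on the propensity covariates are planned, and that a full analysis plan will follow. But naming the variable and the selection rule is a choice made here, and neither the care promised nor the sensitivity analyses mention post-exposure variables.

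Several stronger readings are tempting and are not supported:
- **That place of care certainly enters the propensity score.** The carry-over rule concerns confounders, and the examples do not name it. It may enter.
- **That place of care nearly determines place of death.** The documents give no figure, and the bias does not need one.
- **That the adjusted effect vanishes, or must move towards the null.** An OR of 1.00 requires complete mediation. The shift towards 1 is expected for the marginal weighted OR under mediation; it is not assured for the conditional OR or with unmeasured common causes.
- **That controls would mostly be lost through missing covariates.** Table 1 lists, for the London register, "living circumstances, prognosis, performance status, date and place of death", and does not name living circumstances for the linked North West London data. That description is a summary, not a field list. The missing-data section says only that "individual patients without matching covariate data may be excluded from the multivariable modelling", warns that exclusion could bias the model, and offers imputation.

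**Conclusion.** The point holds as a flaw in a stated analysis choice: the primary and secondary models adjust for place of care without requiring that it precede exposure, although the protocol expects EPaCCS to alter the setting of care. If the value used postdates record creation, the total effect in objective 2A is biased, most likely towards the null for the marginal OR to be reported. From the mid-range 0.39, the OR would be about 0.48 to 1.00 for 25% to 100% mediated. Those figures rest on the protocol's hypothesised rates, a 50:50 exposure split, and assumed mediation shares and stratum risks. If the value is truly pre-EPaCCS, adjustment is legitimate and only the missing time anchor needs repair. In either case the wording should be settled before the outcome data are analysed.

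**What to change.** - Remove place of care from the primary outcome model and the propensity model. Alternatively, replace it with usual residence or care setting recorded before EPaCCS creation, with an equivalent index date for controls.
- State that every covariate in both models takes a pre-exposure value and comes from a source available for both groups. Use carer availability and living circumstances only where that condition is met.
- Use later place of care only in a mediation or sensitivity analysis, labelled as such.

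The cost is mainly wording in the protocol and analysis plan. Some covariate information is lost. If place of care is dropped with no baseline replacement, a real confounder could go with it, which favours the replacement where the data allow. Controls have no EPaCCS creation date, so an index date must be defined for them, and that choice should itself be tested in a sensitivity analysis.
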